**Original Trial Protocol and Statistical Analysis Plan**

Purpose of the Study

Objectives & hypotheses to be tested

The objective of this study is to determine how a Well-being Collaborative web-based seminar series, and online resilience tools, in full or in part, will impact individual well-being. Efficacy of the resilience sessions and tools will be assessed using psychometrically validated survey scales of burnout, depression, happiness, work life balance, disruptive behaviors, emotional thriving, emotional recovery, optimism and state-based anxiety.

The primary hypothesis is that the web-based series and tools will improve individual measures of burnout, depression, happiness, work life balance, disruptive behaviors, emotional thriving, emotional recovery, optimism and state-based anxiety when comparing pre-intervention and post-intervention matched data. We further hypothesize that individual improvements will have a spillover effect on aspects of the shared work environments including disruptive behaviors.

Background & Significance

Should support the scientific aims of the research

Burnout syndrome is a work-related psychopathology comprised of emotional exhaustion, cynicism and inefficacy, which occurs in professionals who do “people work.” Burnout develops from chronic exposure to interpersonal stressors – such as frequent interactions with individuals plagued by complex physical, psychological and social problems. Burnout is also perpetuated by unsupportive or inadequate work environments. Healthcare workers are uniquely vulnerable to burnout as the complex physical crises of patients are often accompanied by equally complex psychosocial and spiritual crises of the individuals and their families. Burnout has been associated with low job satisfaction, absenteeism, poor staff retention, low staff morale, poor performance, disturbed sleep, poor health outcomes and even higher all-cause mortality.

The prevalence and severity of burnout syndrome in healthcare workers is under-recognized as a significant factor affecting the quality and safety of care. The prevalence of burnout in healthcare workers ranges from 27-86%. More alarming is the correlation between burnout and sub-optimal patient care and medical errors. Despite the need for interventions to reduce healthcare worker burnout, few exist.

In recent assessments of unit culture across the Duke University Health System, high burnout has paralleled poor patient safety and teamwork norms across 440 clinical areas. Not surprisingly, this pattern is also seen in other health systems the Duke Center for Healthcare Safety and Quality collaborates with across the country. We hypothesize that an intervention focused on resilience training will improve measures of personal well-being (e.g. burnout, depressive symptoms, happiness) and improve teamwork and safety culture. With the hopes of validating this resilience intervention for use elsewhere, we chose to conduct a formal research study. (see Research Summary document for references)

## Design & Procedures

Describe the study, providing detail regarding the study intervention (drug, device, physical procedures, manipulation of the subject or the subject’s environment, etc.). Discuss justifications for placebo control, discontinuation or delay of standard therapies, and washout periods if applicable. Identify procedures, tests and interventions performed exclusively for research purposes or more frequently than standard of care. Include alternative therapies, concurrent therapies discontinued per protocol, risk benefit ratio, and use of tissue/specimens. Discuss monitoring during washout periods if applicable. Include brief description of follow-up, if any.

This is a study of individuals 18 and over who voluntarily enroll in a web-based well-being series and participate in surveys to assess the effect of the intervention. The intervention will not involve patients, tissues/specimens, drugs, devices, or placebo controls.

## Resilience Collaborative Web-based Series

The Resilience Collaborative Web-based series is a condensed version of the two day “Enhancing Caregiver Resilience: Burnout & Quality Improvement Course” offered by the Duke Center for Healthcare Safety and Quality since 2009. The webinar series is commonly referred to as WISER, short for Web-based Implementation for the Science of Enhancing Resilience. WISER is offered in three formats, full, condensed, and 4-day. The full format of WISER consists of either 12 or 24 webinars, approximately 60 minutes in length each. The condensed format of WISER consists of 10 minute pre-recorded videos using the same content, just offered in smaller chunks. For work settings that afford little logistical opportunity to watch an hour-long video, like NICUs or busy primary care

practices, the condensed format of WISER is recommended. For work settings that have continuing education windows or more logistical flexibility, the full format of WISER is recommended. The most recent version, the 4-day format of WISER, involves 4 consecutive days of 1-hour live or recorded webinars.

WISER is also offered via a randomized control trial design to assess the 5-day format. This format, called WELL-B, introduces participants to a subset of topics in the full WISER format- specifically four of the WISER tools, 1 per day (i.e., Work-life balance, Gratitude, Self-compassion, and Awe). This RCT will occur in the context of a 5 day webinar training. Enrollees will be randomized during electronic informed consent in Qualtrics to either cohort 1 (M-Th) or cohort 2, which occurs the following week (M-Th) via webinar. For those assigned to cohort 1, assessments will occur the first day of the training and day 8 (1-week after the training) as well as 1, 6, and 12 month follow-ups. For those assigned to cohort 2, assessments will occur on their first day of training (day 8 of cohort 1), 1 week after the training, and at 1, 6, and 12 month follow-ups. The RCT comparison will assess tool efficacy between the cohort 1 (week 1) and cohort 2 (week 2). Follow-ups will examine the long term efficacy of the tools.

Another randomized control design of WISER will specifically look at the "Looking Forward" WISER tool.

The Looking Forward Tool asks participants to "Think about something you hope to experience or are looking forward to 3 years from now. ..." and describe what you are looking forward to in 3-4 sentences. Participants will be recruited by the same current method: learning about the tools in a continuing education offering or newsletter, and enrolling through a link on our website. Participants will complete baseline measures and be randomized to either begin the tool immediately (cohort 1), or wait 4 days to begin (cohort 2). Both groups will be assessed on day 4 (waitlist group/cohort 2 will be assessed before they begin the tool). Cohort 1 will continue on with the tool 3 more days; once initiated, the tool is 7 days total for both groups. The RCT comparison will assess treatment efficacy between 4 days of the tool (cohort 1) to the waitlist group (cohort 2). Both groups will be assessed at 1 and 6 month follow-ups for long term efficacy.

We also offer WISER through an observational arm, whereby investigators seek to optimize the number and sequence of WISER modules. The observational arm is intended to help us understand which components of WISER have the biggest and most enduring impact on well-being across different healthcare delivery settings, demographic groups, as well as which modules should be offered earlier in the series so as to maximize participation and improvement in well-being.

The full, condensed, and 4-day versions of WISER were created according to evidence-based principles of adult learning, combining educational material with practice-based learning. We demonstrate the need using evidence of the prevalence and severity of burnout, then the evidence regarding the efficacy of the specific tool being covered, then present the tool for practice-based learning.

Module content WISER condensed: The condensed version of WISER consists of pre-recorded videos, each under 10 minutes in length, playable during use of the tool. The videos are highly refined to be engaging, evidence based, and practical as a launch to the subsequent reflective activity using very brief and enjoyable applications of the module content.

Module 1. Thematic Introduction prevalence of burnout, evidence of enhancing resilience and overview of the next 6 modules.

Module 2. Gratitude: This module provides a structured opportunity to learn about the science behind gratitude tools and express gratitude in general and toward others through a guided gratitude letter writing exercise\). Through expressing gratitude, we learn more about our vital connections to others, often in surprising and meaningful ways, and we see improvements in well-being, sleep quality and depression.

Module 3. Three Good Things: This module introduces a structured opportunity to cultivate positive experiences by reflecting on them for a couple of minutes within two hours of sleep onset (daily email/SMS sent to each participant for 2 weeks). By savoring good moments from earlier that day just before sleep onset, we see improvements in well-being, sleep quality, relationships, work-life balance, and depression.

Module 4. Awe: This module provides a structured opportunity to learn about and experience the benefits of awe and wonder through a series of visually and conceptually stunning images, followed by an exercise to recount in detail one of their own experiences of awe and a daily “moment of awe” log. Participants are encouraged to share moments of awe with others and elicit their moments of awe as an opportunity to connect with others. When we experience awe, our sense of time expands, we are kinder to others, and we prefer experiences over material things. By cultivating awe we see improvements in life satisfaction, kindness, and sense that we have more time to do the important things in life.

We give participants the option to submit photos to us, via qualtrics, that evoke or represent a sense of "awe" to them. We will not share these photos with other participants and the photos will be saved on a secure server. The photos provide a visual focus for the awe exercise that can also be completed using a memory if the participant chooses.

Module 5 Identifying and Using Signature Strengths: This module uses a strengths-finder tool to examine what you do well, and sends daily prompts for one week to elicit how participants will be deliberate about using their strengths in new and more frequent ways to address their challenges. When you use your strengths personally and professionally, you feel engaged and invigorated, and you feel like what you are doing has more meaning to you personally. By deliberately choosing to do what we already do well, we see improvements in engagement, happiness and depression.

Module 6. Random Acts of Kindness: This module uses a nightly log of acts of kindness for 8 days. By committing to random acts of kindness and savoring them later through the use of a log, participants experience temporary but noticeable increases in subjective well-being.

Module 7. Relationship Resilience/ One Good Chat: This module uses 8 days of brief reflections on warm and uplifting interactions as for a strategy to enhancing well-being by savoring brief positive interactions with others.

Module 8. Looking Forward Module. This module asks participants to write reflections about what they are looking forward to at various point in their life - the near future and many years down the road. Research shows that people spend a considerable time envisioning future prospects, but often times this thinking can include worries or fears, rather than what they are looking forward to. This module is to help individuals envision positive events in the future to potentially evoke a feeling of hope rather than worry.

Module 9. Positive Emotion Tracking. This module asks participants to rate the frequency and/or intensity of their emotions, including various positive emotions. Research shows that people with a ratio at or above approximately 3

positive emotions to every 1 negative emotion are more likely to be thriving in their lives. By reporting on their emotions over time, we expect participants to become more aware of their emotions and to engage in behavior that increases their positive emotions, and potentially decreases their experience of negative emotions.

Module 10. Mindfulness Moment. Research has shown that mindfulness meditation confers a variety of salutary effects. This tool will guide participants through a brief mindfulness break (between 1-3 minutes) in which they will focus on the present moment.

Module 11. One Door Closes, Another Opens. Positive reappraisal of difficult experiences is a cognitive mechanism for coping and wellbeing. This tool asks participants to briefly write about any benefits (in the short or long term) that may have resulted from an experience which at first appeared entirely negative.

Module 12. Three Funny Things. Similar in structure to the Three Good Things tool, Three Funny Things asks participants to record funny things that happen each day for 8 days. Research in other labs has identified that doing so improves well-being. It is thought that by being asked to recall funny things prompts the participant to view ongoing experiences through a more humorous lens.

Module 13. The Sleep Tool. This tool asks participants to record each morning for 8 days one's sleep quantity and quality. Evidence-based sleep strategies are prompted each day, such as use of screens, naps, caffeine, and exposure to blue light from sunrises and sunsets. We've found in our research that reflecting on these behaviors appears to improve them over time.

Module 14. Interest Tool. The interest tool was built off research linking curiosity to well-being. It asks participants "What is interesting to you lately?" and to write about it for a couple of minutes. The tool is repeated 4 times over the course of a week.

Module 16. Feedback Tool. This tool will allow participants to report on and track the feedback that they are providing to others, the amount of feedback that they receive, and the amount of feedback that they view occurring between their colleagues.

Module 17. Prioritizing Positivity Tool. In this tool participants are asked to set an intention or goal to participate in activities that give them joy or other positive emotions. The tool encourages achievement in setting this goal and making it a habit by selecting activities that are easy to fit into participants' schedules. This tool is built off of research by [name] that finds prioritizing positive experiences is an effective route to happiness.

Module 18. Your Burnout Story (Expressive Writing) Tool. Inspired by research on the benefits of expressive writing to process difficult emotions, this tool asks participants to write the story of any experiences they've had with burnout. The idea is to process the experience of burnout, reflect on the factors that lead up to it, and provided relief from it, and take lessons from the writing process.

Module 19. Self-compassion Tool. This tool asks participants to reflect on a personal experience they found difficult and that they were overly self-critical about. Next, participants are asked to imagine they were speaking to a good friend about the incident, and to discuss it in a more self-compassionate light.

Module 20. Cultivating Forgiveness Tool. This tool asks participants to reflect on a personal experience where they were wronged and would now like to cultivate forgiveness. Participants are asked to spend 5-7 minutes writing a letter of forgiveness.

Module 21. Pride Tool. The pride tool was built off research linking pride in one's accomplishments to well-being. It asks participants "What is an example of something you deem to be "Fridge-worthy" as in an accomplishment that you would have put on the refrigerator in your kitchen?" and to write about it for a couple of minutes on the screen that has a background image of a large refrigerator. The tool is repeated one week later.

Module 21. Serenity Tool. The serenity tool was built off research linking the positive emotion of feeling at peace with the world around you to well-being. It asks participants to choose a moment when they have 2 minutes without interruption, for example in the car before driving home from work, and to commit to doing nothing for those two minutes. The tool is repeated daily for 8 days.

Module 22. Cultivating Inspiration Tool. This tool asks participants to reflect on people, images, and events that fill them with a positive desire to do good in the world. Participants are asked to spend 5-7 minutes writing a letter of inspiration first, and then again 1 week later.

Module 23. Cultivating Love Tool. This tool asks participants to reflect on people that recharge their batteries and to spend 5-7 minutes writing a letter of what their relationship means to them in detail, then are asked to do it again 1 week later.

Module 24. The Work-life Balance Tool. This tool asks participants to reflect on work-life balance behaviors and activities for 4 days. Behaviors include exercise, spending time with a friend or loved one, spending time in nature, etc. We've found in our research that reflecting on these behaviors appears to improve work-life balance over time.

Module 25. The Grief Tool. This tool asks participants to reflect on a loss they have experienced (e.g., a loved one, a pet, a job, a divorce, etc.). They briefly write about the loss, then engage in a letter-writing activity in which they write from the perspective of a loved one offering them support.

Module 26. The Coaching Tool. This tool asks participants to pause and reflect on their own well-being as well as the well-being of their teams. Participants engage in 5 coaching interactions and complete reflective exercises.

To maximize convenience for research subjects, the recordings will be available for individual viewing over the web and can be viewed individually or shared for group viewings depending on staff and provider availability.

Module content WISER full version: The full version of WISER consists of 12 videos (up to 24 total if the participant chooses to continue another year), approximately 55 minutes in length each, given over 12 months. The brief version of WISER includes videos that are 2-10 minutes in length, and contains the most important elements of the full videos. The videos are highly refined to be engaging, evidence based, and practical as a launch to the following fourteen days of behavioral modification using very brief and enjoyable applications of the module content.

The topics for each WISER full format web-based session, in chronological order, include: Prevalence & Severity of Burnout: Workforce Resilience as Care Quality, Enhancing Resilience: The Science and Practice of Gratitude, Relationship Resilience: The Science of How Other People Matter, Enhancing Resilience: Three Good Things, Enhancing Resilience: Practicing Safe Stress and the Science of Sleep, Psychological Safety: The Predictive Power of Feeling Supported When Things Go Wrong, The Science of Mindfulness, Health Care Worker Resilience, Work Life Integration, and Burnout, Collaboration vs. Dealing with Difficult Colleagues: Assessing, Understanding and Improving Teamwork in a Clinical Area Near You, Science of Wow: Cultivating Awe and Wonder as a Resilience Strategy, Positive WalkRounds: Leader Rounding to Identify What is Going Well – Links to Quality, Culture and Workforce Resilience, Enhancing Resilience: Survival of the Kindest, If Culture Eats Strategy for Lunch, Burnout Eats Culture for Breakfast: New Evidence About the Contagion Effect of Burnout and Impact on Safety Culture, The Funny Thing about Resilience: Evidence for Humor, Improvement Readiness in Healthcare: Introducing a Metric that assesses the capacity within a work setting to start and sustain quality improvement efforts, Coping with Change and the Neuroscience of Hope, Signature Strengths at Work, Second Victim of Harm: Coping After Things Go Wrong, The Surprisingly Robust Science of Self Compassion, Institutional Resources vs. Individual Resources as Solutions for Healthcare Worker Well-Being, Overview of Team Training, Tools, Techniques and Integration into Existing Infrastructure, Absence of Burnout is not the same as Thriving: Moving from Deficit Metrics to Flourishing Metrics for Healthcare Workers, Patient Safety Leadership WalkRounds: Links Safety Culture, Burnout and Workforce Well-Being, The Pursuit of Happiness: Methods vs. Mythology. To maximize convenience for research subjects, the recordings will be shared with unit managers who will coordinate multiple viewings for their clinical areas, based on staff and provider availability.

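### In WELL-B and Looking Forward the waitlist is treated before every long-term follow-up, so those visits cannot show long-term efficacy

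*Protocol*

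**What the plan says.** Both randomised trials are described in the protocol under Design & Procedures, Resilience Collaborative Web-based Series.

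- **WELL-B.** Enrollees are randomised to "either cohort 1 (M-Th) or cohort 2, which occurs the following week (M-Th) via webinar". The schedule of the group trained first reads: "assessments will occur the first day of the training and day 8 (1-week after the training) as well as 1, 6, and 12 month follow-ups". The waitlist group's schedule, whose last three visits are likewise counted in months, reads: "assessments will occur on their first day of training (day 8 of cohort 1), 1 week after the training, and at 1, 6, and 12". The randomised comparison is cohort 1 against cohort 2. A separate sentence then states: "Follow-ups will examine the long term efficacy of the tools".
- **Looking Forward.** Cohort 1 starts the tool at once and cohort 2 waits 4 days. Both are assessed on day 4, cohort 2 before it starts, and "once initiated, the tool is 7 days total for both groups". The randomised comparison is 4 days of tool use against the waitlist. Then: "Both groups will be assessed at 1 and 6 month follow-ups for long term efficacy".

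On other controls, the opening of Design & Procedures says: "The intervention will not involve patients, tissues/specimens, drugs, devices, or placebo controls".

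**The concern.** The protocol uses the word efficacy both for the short randomised comparisons and for the visits months later, without qualification. Efficacy is a causal claim: it needs to be known what the participants would have scored without the tool. In both trials the group that supplies this information is itself treated within days, well before the first long-term visit.

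The stated aims make the claim consequential. Purpose of the Study builds the primary hypothesis on matched before-and-after data, and Background & Significance hopes to validate the intervention for use elsewhere. An uncontrolled change over 6 or 12 months could therefore be read as proof of a lasting effect.

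**Working it through.** The protocol gives no effect size, SD, retention figure or sample-size calculation for either trial, so there is no planned figure to reproduce. The check rests on the schedule. The numerical illustrations use assumed values, marked as such.

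**1. Is anyone untreated at the long-term visits?**

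WELL-B: let day 1 be cohort 1's first Monday. Monday to Thursday gives training on days 1–4 for cohort 1 and days 8–11 for cohort 2. The protocol does not say whether follow-up is counted from a common start or from each cohort's own start, so both are shown.

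| Visit | Days added | Common start: study day | Days since cohort 2 finished | Own start: cohort 2 study day | Days since cohort 2 finished |
|---|---|---|---|---|---|
| 1 month | 30 | 31 | 31 − 11 = 20 | 8 + 30 = 38 | 27 |
| 6 months | 182 | 183 | 183 − 11 = 172 | 8 + 182 = 190 | 179 |
| 12 months | 365 | 366 | 366 − 11 = 355 | 8 + 365 = 373 | 362 |

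Looking Forward: cohort 2 starts after 4 days and uses the tool for 7, so it finishes near day 4 + 7 = 11. The 1-month visit, near day 30, is about 30 − 11 = 19 days later, and the 6-month visit about 182 − 11 = 171 days later.

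Nobody who follows either schedule is untreated at any long-term visit.

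**2. Is there another untreated group?** None is described. There is no placebo control, and participants in the observational arm (Individual Module Survey) use the tools as well.

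**3. What could a between-cohort contrast show at those visits?** Assume an effect of 0.30 SD that decays with half-life H. On a common calendar the contrast is 0.30 × 2^(−t1/H) − 0.30 × 2^(−t2/H), where t1 and t2 are the days since each cohort finished.

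- At 1 month t1 = 31 − 4 = 27 and t2 = 20. With H = 30 days this is 0.161 − 0.189 = −0.028 SD.
- At 12 months, as H goes from 30 days to no decay, the true effect against no treatment runs from 0.000 to 0.300 SD. The contrast stays between 0 and −0.002 SD.
- Counted from each cohort's own start, the contrast is 0 throughout.

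The contrast is near zero whether or not the effect lasts.

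**4. What could within-person change show?** With no true effect, regression to the mean produces an apparent improvement of s × (1 − r). Here s is how much worse than their long-run mean participants are at entry, and r is the test-retest correlation; both are assumed.

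- s = 0.25 SD, r = 0.8: 0.25 × 0.2 = 0.05 SD.
- s = 0.50 SD, r = 0.5: 0.50 × 0.5 = 0.25 SD.

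Time trends over 6 or 12 months add to this in an unknown direction. Selective retention adds (1 − response rate) × (difference in change between responders and non-responders). The protocol supports no value for either term, so none is put in.

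**The case against.** The best defence is that the protocol already keeps two inferences apart. Each trial has one sentence for the randomised comparison and another for follow-up, and neither says that the follow-up is randomised or controlled. A short waitlist with uncontrolled follow-up is a recognised design. All of that stands, and it is why the point concerns the label on the follow-ups and not the randomised comparisons. It does not rescue the label: persistence or durability could be read descriptively, but efficacy, used for both purposes, cannot.

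The unseen analysis plan is no answer either. It may settle who enters the follow-up analysis and how missing visits are handled, but no analysis restores a comparator that the schedule removes.

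Four stronger readings are tempting and are not supported:

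- *The trials have no untreated comparator at all.* They have one up to cohort 2's first training day in WELL-B and up to day 4 in Looking Forward.
- *The protocol plans to compare cohorts at the long-term visits.* It states no such comparison. Step 3 shows only that one would not help.
- *Dropout biases the follow-up result by a known amount.* The stated analysis uses matched data, so a stable difference in level between responders and non-responders cancels. Bias arises only if their change differs, and Subject Recruitment and Compensation acknowledges attrition without giving a rate.
- *Looking Forward claims randomised evidence for the whole 7-day tool.* It does not; its randomised comparison is openly confined to 4 days of use.

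**Conclusion.** The point holds for the long-term visits of both trials. Controlled follow-up at 1, 6 and 12 months (WELL-B) and at 1 and 6 months (Looking Forward) is zero, against a randomised separation of about 7 and 4 days. The long-term efficacy purpose given to those visits is therefore one that the design cannot serve. The data can describe how scores run after use, but cannot attribute the course to the tools.

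This conclusion rests on the protocol's schedule alone, for participants who follow it. The 0.05 to 0.25 SD from regression to the mean and the near-zero between-cohort contrast are illustrations under assumed values; neither is needed for it. The randomised day-8 and day-4 contrasts are untouched.

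**What to change.** In both trial descriptions, replace the statement of purpose for the follow-ups with: *Follow-ups describe the uncontrolled course of well-being after use of the tools; no efficacy claim is made from them.* In Looking Forward the sentence also carries the visit times, which should be kept.

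Limit efficacy conclusions to the day-8 comparison in WELL-B and the day-4 comparison in Looking Forward. The second is already how the protocol words that trial's randomised comparison.

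Optionally, estimate the follow-up course with a mixed model on all participants who have a baseline. This lessens the dependence on those who still respond, but does not supply a control.

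No visit, questionnaire or participant is lost. The cost is a change of wording and a less favourable long-term claim. A controlled long-term claim would need a comparator that stays untrained through the visit in question, which is a different design.
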